### Outcome measurements

3.4

Study visits will be conducted at baseline and 12, 24, 36, and 48 weeks after initiation of upadacitinib administration. The assessments are presented in Table 1. Clinical physicians will be blinded to joint assessments by MSUS.

**Table 1 T1:**
[figure not shown]
Treatment schedule and outcome measures.

#### Clinical disease activity

3.4.1

Clinical disease activity will be evaluated by each attending physician (Japan College of Rheumatology-certified rheumatologists) based on the values of the DAS28-ESR, DAS28-CRP score, clinical disease activity index (CDAI), simplified disease activity index (SDAI), and the EULAR response criteria.^[11]^ At each visit, 28 joints, including the bilateral glenohumeral, elbow, wrist, metacarpophalangeal (MCP), interphalangeal, proximal interphalangeal of the hand, and knee joints, will be assessed for tenderness and swelling. Global and pain assessment and evaluator global assessment of each patient will be established on a 0–100-mm visual analog scale, and functional assessment will be scored according to the Health Assessment Questionnaire-Disability Index (HAQ-DI).

#### MSUS assessments

3.4.2

Participants will undergo imaging by MSUS at baseline and 12, 24, 36, and 48 weeks. Each MSUS examination will be conducted by a Japan College of Rheumatology-certified sonographer. Systematic multiplanar grayscale (GS) and PD examinations of the joints will be performed using a multifrequency linear transducer (12–24 MHz). PD will be used depending on which Doppler modality of the individual machine is the most sensitive. The Doppler settings will be adjusted at each hospital in accordance with published recommendations.^[12,13]^ There will be no change in the MSUS settings during the study and no software upgrade.

Articular synovitis will be assessed by MSUS at dorsal views of 22 joints, including the bilateral wrist joints, 1st–5th MCP joints, interphalangeal joints, and 2nd–5th proximal interphalangeal joints. Each joint will be scored for GS and PD on a scale of 0 to 3 in a semiquantitative manner. The sum of the GS or PD scores will be considered the total GS or PD score, respectively. The Outcome Measures in Rheumatology-EULAR combined PDUS score (i.e., the combined PD score) and Global Outcome Measures in Rheumatology-EULAR Synovitis score will also be assessed.^[14,15]^ The combined PD score will be combined with synovial hypertrophy as indicated by the GS and PD scores.^[14,15]^

#### X-ray imaging

3.4.3

X-ray imaging of the bilateral hands (posteroanterior view) and feet (anteroposterior view) will be conducted. Joint damage progression will be evaluated based on the van der Heijde-modified total Sharp score (vdH-mTSS) of 16 areas of each hand for erosions and 15 for joint-space narrowing.^[16]^

#### Biomarker measurements

3.4.4

Patient serum concentrations of the following biomarkers will be measured: rheumatoid factor (RF) using the latex agglutination turbidimetric immunoassay (LZ test “Eiken” RF; Eiken Chemical Co., Ltd., Tokyo, Japan). Anti-cyclic citrullinated peptide antibodies will be measured using a chemiluminescent immunoassay (STACIA MEBLux CCP test, Medical and Biological Laboratories, Aichi, Japan). Matrix metalloproteinase-3 will be measured using latex turbidimetric immunoassay (Panaclear matrix metalloproteinase-3 “Latex”; Sekisui Medical Co., Ltd., Tokyo, Japan). Multiplex cytokine/chemokine bead assays will be performed using diluted serum supernatants and the MILLIPLEX MAP Human Cytokine/Chemokine Magnetic Bead Panel (Merck KGaA, Darmstadt, Germany) and the Bio-Plex Pro Human Cytokine Assays (Bio-Rad Laboratories, Inc., Hercules, CA) and analyzed with a Bio-Plex MAGPIX Multiplex Reader (Bio-Rad Laboratories, Inc.) in accordance with the manufacturers’ instructions.

The cytokines/chemokines for measurement with the bead panel will include interleukin (IL)-1α, IL-1β, IL-1 receptor antagonist, IL-2, IL-4, IL-5, IL-6, IL-7, IL-8, IL-10, IL-12 (p40), IL-12 (p70), IL-13, IL-15, IL-17A, IL-17F, IL-18, IL-22, IL-27, interferon (IFN)-γ, IFN-α2, CXC motif (CXC)L1 (growth-related oncogene), granulocyte-macrophage colony-stimulating factor, granulocyte colony-stimulating factor, C-X3-C motif ligand 1 (fractalkine), flt-3 ligand, fibroblast growth factor-2, eotaxin, epidermal growth factor, vascular endothelial growth factor, platelet-derived growth factor-AA, soluble CD40 ligand, TNF-α, TNF-β, transforming growth factor-α, C-C motif chemokine ligand (CCL)4 (macrophage inflammatory protein [MIP]-1β), CCL3 (MIP-1α), CCL22 (macrophage-derived chemokine), CCL7 (MCP-3), CCL2 (MCP-1), CXCL10 (IFN-γ-inducible protein-10), vascular cell adhesion molecule-1, and intercellular adhesion molecule-1.

### Study endpoints

3.5

#### Primary endpoint

3.5.1

The primary endpoint is maintenance of a DAS28-CRP score of ≤3.2 from week 24 to 48 in patients who achieve a DAS28-CRP score of <2.6 at week 24.

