#### Intervention

3.3.3

Patients will receive upadacitinib at 15 mg/day and continue to receive the same dosage of MTX with or without a corticosteroid for 24 weeks (Stage I). If a EULAR-defined moderate response or a DAS28-CRP score of ≤3.2 is achieved at 12 weeks with a DAS28-CRP score of <2.6 at 24 weeks, MTX will be discontinued and upadacitinib with or without a corticosteroid will be continued until week 48 (Stage II). Patients not achieving a EULAR-defined moderate response and a DAS28-CRP score of ≤3.2 at 12 weeks or <2.6 at 24 weeks will be excluded from this study.

During the study period, the following treatments are prohibited: administration of a bDMARD or JAK inhibitor, other than upadacitinib; concomitant use of an immunosuppressant (i.e., azathioprine, cyclophosphamide, or cyclosporine), csDMARD, other than MTX, or an oral corticosteroid equivalent to >7.5 mg/day of prednisolone; intra-articular corticosteroid injections at the joints; and any nonsteroidal anti-inflammatory drug suppository. During the study period, the dosage of any oral nonsteroidal anti-inflammatory drug can be modified within the range approved in Japan.

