#### Patient discontinuation criteria

3.3.4

A patient may be prematurely withdrawn from the study for the following reasons:

Discontinuation of upadacitinib for more than 7 consecutive daysFailure to achieve a EULAR-defined moderate response and a DAS28-CRP score of ≤3.2 at week 12Failure to achieve a DAS28-CRP score of <2.6 at week 24Discontinuation of MTX for more than 2 consecutive weeks during Stage IAny clinical relapse, defined as an increase in a DAS28- erythrocyte sedimentation rate (ESR) score of ≥3.2 due to elevated disease activity of RA, after discontinuation of MTXPatient request to quit the trialPatient request to change or discontinue treatmentAny AE inhibiting continued participationPregnancyDiscretion of the principal investigator to discontinue trial participation to ensure patient safety

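### The primary endpoint scores DAS28-CRP alone, so a Stage II patient given added oral steroid within the cap, or put back on MTX, can count as maintained

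*Protocol article*

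**What the plan says.** Section 3.5.1 defines success on one index: "The primary endpoint is maintenance of a DAS28-CRP score of ≤3.2 from week 24 to 48", among patients in remission at week 24. It attaches no condition on treatment.

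Section 3.3.3 sets the treatment rules:

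- Stage I: patients "continue to receive the same dosage of MTX with or without a corticosteroid for 24 weeks". The constant dose is stated for MTX.
- Stage II: "MTX will be discontinued and upadacitinib with or without a corticosteroid will be continued until week 48". No steroid dose is given.
- Prohibited throughout the study period: "csDMARD, other than MTX, or an oral corticosteroid equivalent to >7.5 mg/day of prednisolone", and also "intra-articular corticosteroid injections at the joints". The MTX exception carries no stage.
- Expressly allowed: "the dosage of any oral nonsteroidal anti-inflammatory drug can be modified within the range approved in Japan".

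The steroid-stability rule among the exclusion criteria (3.3.2) covers only the 4 weeks before consent.

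Section 3.3.4 lists reasons for which a patient may be withdrawn. Among them is "clinical relapse, defined as an increase in a DAS28- erythrocyte sedimentation rate (ESR) score of ≥3.2" after MTX has stopped. Starting or raising a steroid within the cap is not listed, nor is resuming MTX in Stage II.

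On timing (3.4): "Study visits will be conducted at baseline and 12, 24, 36, and 48 weeks after initiation of upadacitinib administration". Stage II therefore has scheduled assessments at weeks 36 and 48 only.

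**The concern.** The primary objective (2.1) is the proportion of patients who stay free of clinical relapse once MTX has been stopped. If disease worsens and is brought back under control with more oral steroid, or with MTX itself, a low DAS28-CRP at the next visit no longer shows that the patient managed without MTX. The endpoint as written cannot tell such a patient from one who stayed well on unchanged treatment.

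The error runs one way. Added anti-inflammatory treatment can turn a failure into a recorded success; it does not turn a success into a failure. In a randomised comparison part of this might cancel between arms. Here the single proportion is the result.

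**Working it through.** **1. Can such a patient be scored as maintained?** Four things must hold in the same patient:

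| Condition | What the article says |
|---|---|
| Disease worsens between scheduled visits | 12-week gaps in Stage II (3.4) |
| Oral steroid is started or raised to at most 7.5 mg/day, or MTX is resumed | Neither is in the prohibited list (3.3.3) |
| The patient is not withdrawn | Neither is a named withdrawal reason; the relapse criterion needs a DAS28-ESR of 3.2 or more (3.3.4) |
| No DAS28-CRP above 3.2 is recorded | Then the endpoint is met (3.5.1) |

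The path is open but narrow. Any recorded DAS28-CRP above 3.2 from week 24 to 48 still fails. A patient already on 7.5 mg/day has no room for an increase, and the intra-articular route is closed.

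**2. The plan's own figures (3.8, 3.9).** The Wilson half-width is z/(1+z²/n) × √[p(1−p)/n + z²/(4n²)], with z = 1.96 and p = 0.65.

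- n = 83: 0.1005. n = 84: 0.09996. So 84 is the smallest n with a half-width of at most 0.10, as stated.
- 84/0.60 = 140, as stated.
- 140/0.90 = 155.6, against the stated 155.

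The planned numbers are sound for this purpose, and the point does not alter them.

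**3. Effect per patient.** 1/84 = 0.0119, or 1.2 percentage points.

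**4. Illustration by count.** Suppose 55 of 84 are recorded as maintained (65.5%, Wilson 95% interval 54.8 to 74.8%). The number treated in this way is an assumption:

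| Recorded successes so treated | Proportion after reclassification | Wilson 95% interval |
|---|---|---|
| 2 | 53/84 = 63.1% | 52.4 to 72.6% |
| 4 | 51/84 = 60.7% | 50.0 to 70.5% |
| 8 | 47/84 = 56.0% | 45.3 to 66.1% |

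**5. Illustration by coverage.** Now assume instead that 0.65 is the true proportion maintained without added steroid or MTX. True failures are then 0.35 × 84 = 29.4. If the recorded success probability is 0.65 + r, the share of true failures that must be hidden is r/0.35. Exact binomial coverage of the 95% Wilson interval at n = 84:

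| r | Share of true failures hidden | Patients (84r) | Coverage of 0.65 | Coverage of 0.65 + r |
|---|---|---|---|---|
| 0 | 0% | 0 | 94.8% | 94.8% |
| 0.01 | 2.9% | 0.8 | 95.0% | 95.0% |
| 0.02 | 5.7% | 1.7 | 94.3% | 95.2% |
| 0.05 | 14.3% | 4.2 | 86.7% | 95.8% |
| 0.10 | 28.6% | 8.4 | 54.2% | 94.2% |

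The last column is for the endpoint exactly as written, and it stays near 95%. Any loss is only against the objective in 2.1. A bias of 1 to 2 points is negligible; 5 points would matter, but needs about one true failure in seven to be hidden in this way.

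**The case against.** The strongest reply is that this is an argument from silence. The article condenses a longer protocol, and steroid dose rules or the handling of treatment changes may be set out there. Section 3.3.3 also has a natural reading under which the dose is fixed: background treatment continues to week 48, and dose changes are expressly allowed only for oral NSAIDs, which suggests that the rest stays put.

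That has weight. A reader might infer that the protocol permits steroid rescue in Stage II. The text does not support this; it neither permits nor bars an increase within the cap. But the article does set out its concomitant-treatment rules and its endpoint, and an analyst applying the endpoint as stated would count these patients as maintained on either reading of the dosing rule. A treatment rule, even a strict one, does not say how a breach is scored.

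Second, the secondary endpoints (3.5.2, item 3) define relapse as DAS28-CRP above 3.2, with no treatment component, so it can be said that the objective never required freedom from added treatment. This stands for the endpoint as written. It is less convincing for an objective framed around stopping MTX, above all where MTX is resumed.

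Third, 0.65 is given in 3.8 as the prediction for the DAS28-CRP endpoint, so treating it as maintenance without added treatment is an assumption. That is correct, and the coverage figures are illustrations only.

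Fourth, the guards are real: the dose cap, the ban on intra-articular steroid, withdrawal for DAS28-ESR relapse, at the patient's request or at the investigator's discretion. They make the group small. They do not name the cases at issue.

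Finally, scoring any increase as failure catches some patients who never crossed 3.2, although the endpoint tolerates movement from below 2.6 up to 3.2. This is a genuine cost of the fix.

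**Conclusion.** The point holds as a modest one, worth considering. The stated endpoint, the cap-only steroid rule and the MTX exemption without a stage limit together allow a patient treated for worsening in Stage II to be scored as maintained. Relative to the objective in 2.1 the direction is upward.

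The size is unknown, because the article gives no rate of steroid increase or MTX resumption. It is probably small, because all four conditions must coincide: 1.2 points per patient, with one or two patients well inside the planned 10-point half-width. A reader might take the 5- and 10-point rows as the expected bias; nothing in the document supports rates that high. A reader might also infer that the Wilson interval is at fault. It is not: for the endpoint as written, coverage stays at about 94 to 96%.

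The conclusion rests on the article's wording as it stands. A rule in the full protocol or analysis plan that scores such patients as failures would settle it.

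**What to change.** - In the primary analysis, count as not maintained any Stage II patient who, before week 48, has oral corticosteroid started or raised above the week 24 dose, resumes MTX, or receives another prohibited anti-rheumatic drug. Exempt a change only where a non-RA indication is documented when the change is made, so that the reason is not judged later with the outcome known.
- Report the DAS28-CRP-only proportion alongside as a sensitivity analysis.
- In the prohibited list in 3.3.3, limit the csDMARD exemption to MTX in Stage I.

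The permitted steroid range, visit schedule and sample size stay as they are. The cost is some wording and one variable derived from concomitant-treatment data. The reported proportion may be slightly lower, and some patients given a small steroid increase without ever exceeding 3.2 will count as failures; the sensitivity analysis shows how many. The indication is still recorded by an unblinded investigator, so requiring it at the time of the change limits that judgement but does not remove it.

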#### Secondary endpoints

3.5.2

The secondary endpoints of this study are as follows: (1) achievement of a DAS28-CRP score of ≤3.2 at weeks 12, 24, and 36; (2) achievement of a DAS28-CRP score of <2.6 at weeks 12, 24, 36, and 48; (3) clinical relapse (DAS28-CRP score of >3.2) at week 48 in patients who achieved a DAS28-CRP score of <2.6 at week 24; (4) achievement of an EULAR-defined moderate response at week 12; (5) changes in DAS28-ESR and DAS28-CRP scores from baseline to weeks 12, 24, 36, and 48; (6) changes in DAS28-ESR and DAS28-CRP scores from week 24 to 36 and 48; (7) changes in CDAI and SDAI values from baseline to weeks 12, 24, 36, and 48; (8) changes in CDAI and SDAI values from week 24 to 36 and 48; (9) achievement of a CDAI of ≤2.8 at weeks 12, 24, 36, and 48; (10) achievement of a SDAI of ≤3.3 at weeks 12, 24, 36, and 48; (11) changes in biomarker serum levels from baseline to weeks 12, 24, 36, and 48; (12) changes in biomarker serum levels from week 24 to 36 and 48; (13) changes in total PD and GS scores and combined PD score from baseline to weeks 12, 24, 36, and 48; (14) changes in total PD and GS scores and combined PD score from week 24 to 36 and 48; (15) change in vdH-mTSS from baseline to weeks 24 and 48; (16) change in vdH-mTSS from week 24 to 48; (17) change in the HAQ-DI data from baseline to weeks 12, 24, 36, and 48; and (18) change in the HAQ-DI data from week 24 to 36 and 48.

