**Methods/design::**

The proposed study is an interventional, multicenter, open-label, single-arm clinical trial with a 48-week follow-up. The cohort will include 155 RA patients with at least moderate disease activity during treatment with MTX. Patients will receive upadacitinib and MTX will be discontinued for those who achieve clinical remission. Disease activity will be evaluated longitudinally by measuring clinical disease activity indices and with musculoskeletal ultrasound (MSUS). The primary endpoint is the proportion of patients who sustain a disease activity score-28- C reactive protein score of ≤3.2 from week 24 to 48 after a disease activity score-28- C reactive protein score of <2.6 at week 24. Important secondary endpoints are changes from baseline MSUS scores. Serum levels of multiple biomarkers, including cytokines and chemokines, will be comprehensively analyzed.

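### Secondary endpoint (3) counts relapse only at week 48, although patients may be withdrawn for relapse before then, so as worded it understates relapse

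*Protocol article*

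**What the plan says.** All places are in the protocol article.

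- **Secondary endpoints (3.5.2), item 3:** "3) clinical relapse (DAS28-CRP score of >3.2) at week 48 in patients who achieved a DAS28-CRP score of <2.6 at week 24". Relapse is a status at one visit, by DAS28-CRP, in a named population.
- **Patient discontinuation criteria (3.3.4):** the list opens with "A patient may be prematurely withdrawn from the study for the following reasons". One reason is clinical relapse after MTX is stopped, defined there by DAS28-ESR at or above 3.2.
- **Outcome measurements (3.4):** visits are at baseline and weeks 12, 24, 36 and 48, so week 36 is the only scheduled visit inside Stage II before its end.
- **Primary endpoint (3.5.1):** DAS28-CRP at or below 3.2 must be maintained over the whole interval from week 24 to week 48, in patients below 2.6 at week 24.
- **Intervention (3.3.3):** patients who miss the response criteria "at 12 weeks or <2.6 at 24 weeks will be excluded from this study". This wording is definite, unlike the permissive opening of 3.3.4.
- **Other secondary endpoints (3.5.2):** several run past week 24 with no population named, for example "achievement of a DAS28-CRP score of <2.6 at weeks 12, 24, 36, and 48" and "changes in total PD and GS scores and combined PD score from baseline to weeks 12, 24, 36, and 48". The abstract says: "Important secondary endpoints are changes from baseline MSUS scores".
- **Statistical analysis (3.9):** an analysis set is stated for the primary endpoint only.

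**The concern.** The event that endpoint (3) is meant to count is also a reason for leaving before the visit at which it is counted. A patient who relapses at week 36 and is withdrawn has no scheduled week 48 value. Read literally, that patient either drops out of the calculation or stays in the denominator without an event. Both readings lower the relapse figure. On the primary endpoint the same patient can be a failure, so two endpoints describing loss of control in the same patients can differ merely because of how one is timed. Relapse after stopping MTX is the question the trial exists to answer, so a too-favourable relapse percentage next to the primary result would mislead.

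The relapse definitions also differ. Withdrawal uses DAS28-ESR at or above 3.2, and the endpoint uses DAS28-CRP above 3.2. A patient can be withdrawn for relapse without meeting the endpoint's definition and then have no week 48 value.

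A lesser point of the same kind concerns endpoints measured from baseline. By weeks 36 and 48, those who failed the week 12 or week 24 criteria have left, so these endpoints describe only patients selected for response, and the list does not say so.

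**Working it through.** **Inputs, all from Sample size (3.8):** expected primary proportion 0.65 with a 95% CI half-width of 0.10; 84 patients at the start of monotherapy; 60% reaching DAS28-CRP below 2.6; 140 at the start of combination therapy; 10% dropout; target 155.

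**Step 1: reproduce the plan's figures.** The Wilson half-width is z/(1+z²/n) × √(p(1−p)/n + z²/(4n²)). With p = 0.65 and z = 1.96 it is 0.1005 at n = 83 and 0.1000 at n = 84, so 84 is confirmed. Then 84/0.60 = 140, and 140/0.90 = 155.6, against the stated 155. The sample size does not depend on this point.

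**Step 2: endpoint (3) as worded.** Expected non-maintenance is 0.35 × 84 = 29.4 patients. Let f be the share of these withdrawn before week 48. The article does not give f, so a range is shown. Further assumptions: all 29.4 are relapses under both definitions, those not withdrawn are in relapse at week 48, and there is no other dropout.

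- Among patients observed at week 48: 29.4(1−f) / (84 − 29.4f)
- All 84 in the denominator, earlier relapses uncounted: 29.4(1−f) / 84
- Withdrawal for relapse counted as an event: 29.4/84 = 35% for every f

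| f | Observed at week 48 | All 84, early relapses uncounted | Withdrawal counted |
|---|---|---|---|
| 0 | 35.0% | 35.0% | 35% |
| 0.25 | 22.05/76.65 = 28.8% | 22.05/84 = 26.25% | 35% |
| 0.50 | 14.7/69.3 = 21.2% | 14.7/84 = 17.5% | 35% |
| 0.75 | 7.35/61.95 = 11.9% | 7.35/84 = 8.75% | 35% |
| 1 | 0% | 0% | 35% |

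In whole patients (29 relapsers, of whom 7, 14 or 22 leave early), the observed-case values are 22/77 = 28.6%, 15/70 = 21.4% and 7/62 = 11.3%.

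**Step 3: endpoints with no named population.** The plan expects 140 − 84 = 56 of 140 (40%) to miss remission and leave by week 24. For maintained response, 65% of Stage II entrants corresponds to 0.60 × 0.65 = 39% of those starting Stage I. The base is 140, because 155 also contains the allowance for ordinary dropout.

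This step reaches two groups:

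- the achievement endpoints (1) at week 36 and (2), (9) and (10) at weeks 36 and 48;
- the changes from baseline (5), (7), (11), (13) and (17) at weeks 36 and 48, and (15) at week 48.

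It does not reach (6), (8), (12), (14), (16) and (18), which start at week 24.

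**The case against.** The strongest reply has four parts.

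**Handling of withdrawn patients belongs in the SAP or the full protocol, and neither is shown.** This stands for denominators in general, for models of change scores and for whether data are collected at withdrawal (Table 1 is not readable). Nothing in the article says that the secondary endpoints are restricted to completers, so a reader who infers that goes beyond the text. It does not dispose of endpoint (3), where the article itself fixes the time point. An SAP could count an earlier relapse only by departing from that wording.

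**Withdrawal for relapse is optional and uses a different index.** This also stands. A reader might infer that everyone who relapses before week 48 lacks a week 48 value, or that endpoint (3) catches only first relapses falling at week 48. The permissive wording and the DAS28-ESR criterion do not support either. Optional withdrawal makes the size of the understatement uncertain, but its direction stays the same.

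**The primary endpoint already covers relapse at any time.** True, and the redefined endpoint (3) would be close to its complement. Nor must the present endpoint (3) contradict the primary result: an interval measure and a status at one visit need not sum to 1. The trouble is that part of the gap would come from withdrawals and not from disease course, and a reader could not tell which.

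**Removing non-remitters defines the target population.** Correct for the primary endpoint, for endpoint (3) and for the series starting at week 24. It is no answer for endpoints measured from baseline that name no population. A reader might also infer that the MSUS changes highlighted in the abstract are biased as a whole. The abstract does not single out weeks 36 and 48, and the week 12 scan precedes any exclusion for non-response.

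**Conclusion.** The point holds for endpoint (3). Its stated time point, combined with relapse as a ground for withdrawal, understates relapse whenever a relapsing patient is withdrawn before week 48. If half of the expected relapsers leave early, the observed-case figure is 21.2% instead of 35%. That gap of 13.8 percentage points exceeds the 10-point half-width the trial is sized for. With a quarter leaving early the gap is 6.2 points, and with none it is zero. The result rests on the plan's 0.65 and 84, on an early-withdrawal share that the article does not give, and on the simplifying assumptions stated above.

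The conflict between the DAS28-ESR and DAS28-CRP relapse definitions is in the text and needs no assumption.

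The point about unnamed populations is secondary and one of labelling and denominators. Neither the sample size nor the primary endpoint is affected by the exclusion of non-remitters, and the article calls all analyses other than the primary exploratory. This should be corrected, but it does not undermine the main result.

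**What to change.** 1. Define endpoint (3) as relapse at any time after week 24 up to week 48 among all Stage II entrants, with withdrawal for relapse counted as an event.
2. Reconcile the relapse definition in section 3.3.4 (DAS28-ESR at or above 3.2) with that in section 3.5.2 (DAS28-CRP above 3.2). Until that is done, counting withdrawals as events would mix two indices in one endpoint. Which definition to use is for the investigators.
3. For each week 36/48 endpoint without a named population, state that it describes Stage II patients. For the achievement endpoints (1), (2), (9) and (10), the alternative is to keep all treated patients in the denominator and count withdrawal for non-response or relapse as not achieved.

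The cost is wording in the endpoint list and the SAP, with no change to treatment or sample size. The stated rates become less favourable, and endpoint (3) moves close to the complement of the primary endpoint.
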